# Implementation evaluation of an evidence-informed hospital inpatient nursing framework (HIRAID® Inpatient): a protocol for a stepped-wedge cluster RCT

**DOI:** 10.1186/s13063-025-09313-8

**Published:** 2025-12-04

**Keywords:** Evidence-based nursing, Nursing assessment, Behaviour change, Clinical deterioration, Communication, Adverse events, Quality of health care, Health services research, Implementation science

## Abstract

**Background:**

Preventable adverse events in Australian hospitals are a significant safety issue, causing harm, death and increased healthcare costs. Many stem from inadequate recognition of, or response to, clinical deterioration by nurses that suggest gaps in current nursing practice frameworks. Responding to health sector demand, this study will adapt the evidence-informed HIRAID® nursing framework for use in hospital inpatient settings, implement and evaluate the standardised HIRAID® Inpatient framework to improve the quality and safety of inpatient hospital care.

**Methods:**

HIRAID® will be adapted for the hospital inpatient setting using a real-time Delphi technique and co-design with frontline hospital inpatient nurses, consumers, managers, physicians and allied health clinicians (Phase 1). An explanatory mixed methods study incorporating staff surveys and focus groups, informed by behaviour change theory, will be used to generate the implementation strategy (Phase 2).

The intervention will be trialled with 1259 nurses from 35 inpatient wards (10 hospitals) across three health services in two Australian states, using a Type II hybrid effectiveness-implementation design, including a Stepped-Wedge clustered Randomised Control Trial (Phase 3). There will be four clusters, determined by geography and clinical governance, where 4050 patients are admitted per month. These clusters were selected due to their direct admission of acutely unwell patients that are at a high risk of experiencing adverse events.

Routinely collected data, guidance documents, and pre- and post-intervention surveys of patients, carers, nursing and medical staff will be used to test the seven study hypotheses. Sample size calculations were based on prior research, assuming a 3% intra-class correlation, 5% significance (two-tailed) and 80% power, and using Woertman’s Stepped-Wedge estimate approach. Evaluation of implementation and fidelity will be assessed using the RE-AIM framework. Outcomes of interest include rates of preventable nurse-associated clinical deterioration, hospital-acquired complications, patient and carer experiences with care, and quality of nursing documentation and communication.

**Discussion:**

HIRAID® Inpatient aims to optimise nurses’ contribution to the quality and safety of hospital nursing care by preventing adverse events, improving patient experiences and strengthening clinical communication through a standardised, evidence-informed framework for assessment, decision-making and action.

**Trial registration:**

Australian and New Zealand Clinical Trial Registry, ACTRN12625000639426. Registered on 17 June 2025, https://anzctr.org.au/ACTRN12625000639426.aspx.

**Protocol version:**

Version 5.0 30 April 2025.

**Supplementary Information:**

The online version contains supplementary material available at 10.1186/s13063-025-09313-8.

## Introduction

### Background

Preventable adverse events in Australia’s hospitals, such as clinical deterioration and hospital-acquired complications (HACs), are a major ongoing safety issue [1]. These events can result in patient harm, mortality, increased length of stay, increased financial and resource burden for hospitals, and negative patient and family experiences [2]. They are, however, largely preventable [3]. Despite the widespread implementation of rapid response systems that facilitate early recognition and response to deteriorating patients, rates of clinical deterioration and HACs remain static, often due to delays or failures in recognition and/or response to clinical deterioration [4]. Up to 80% of rapid response team (RRT) calls are preceded by objective signs of clinical deterioration present for many hours before RRT activation [5].

Current patient assessment frameworks used by nurses’ target deviations in vital signs, the assessment of specific body systems, identification of specific risks (e.g. falls, pressure injuries, delirium) and recognition of the deteriorating patient [6]. Although useful, the piecemeal use of these frameworks hinders nurses’ capacity to perform a thorough assessment of the entire patient status [7], which, in turn, does not prevent patient deterioration [8]. With improvements to patient assessment frameworks, inpatient nurses could better address the increasingly complex health and well-being needs of patients.

Nurse-led frameworks that improve patient outcomes in emergency care, improve the quality of clinical assessment of patients [9], and reduce urinary tract infections [10]. However, a review of the international literature shows the absence of a standardised, evidence-based nursing framework for nurses in hospital wards or inpatient settings [8]. Moreover, a large evidence-based nursing core assessment, the ENCORE Queensland trial (2024), underscored the necessity to strengthen nursing assessment for complex patients in hospital wards [11]. To be successful, an inpatient nursing framework must facilitate the assessment of the entire patient [8]. We propose a new ‘whole-of-patient’ nursing framework that can be tailored to any hospital inpatient setting.

### Rationale

Despite considerable attention existing inpatient assessment nursing frameworks are not optimising efforts to prevent clinical deterioration. In Australian hospital wards, nurses’ approaches to, and practices of, patient assessment are inconsistent, resulting in significant avoidable patient deterioration and unwarranted variation in care [8].

The aim of this paper is to describe the methods to be used to address nurses’ inconsistent approaches to, and practices of, patient assessment by adapting the eight-element HIRAID® framework (History including Infection risk, Red Flags, Assessment, Intervention, Diagnostics, reassessment, communication and plan) for the inpatient context. HIRAID® was first developed for emergency departments (ED) and provides a holistic and structured approach to nursing assessment and management that improves the quality and consistency of nurses’ judgement, practice and documentation (Fig. 1). In EDs, HIRAID® significantly improved nurses’ clinical care, documentation and handover. HIRAID® also significantly decreased patient deterioration related to nursing care, treatment delays, failure to escalate care of deteriorating patients and resulted in healthcare cost avoidance [7, 12–14]. With adaptation of HIRAID® ED for the inpatient setting, we envisage similar benefits for inpatient settings.

**Fig. 1 Fig1:**
[figure not shown]
Preliminary conceptual framework for HIRAID® Inpatient

#### Study design

Implementation and evaluation of HIRAID® Inpatient will be undertaken in three phases (Fig. 2). In Phase 1, the existing HIRAID® emergency nursing framework will be adapted and recontextualised for inpatient care using a pragmatic modified Delphi technique. In Phase 2, an explanatory sequential mixed methods study design will use behaviour change theory-informed surveys of nursing staff to determine “who needs to change what” to implement inpatient HIRAID®. Focus group interviews will further determine barriers and enablers to implementation. A modifiable implementation strategy will be developed for each cluster. In Phase 3, the finalised framework and implementation strategy will be evaluated with a Type II effectiveness-implementation hybrid design, including a stepped-wedge cluster randomised control trial (SW-cRCT), conducted in 35 wards from 10 hospitals in New South Wales (NSW) and Victoria, Australia.

**Fig. 2 Fig2:**
[figure not shown]
Overarching study design and methods for HIRAID® Inpatient

## Methods: participants, interventions and outcomes

### Phase 1: Delphi study—adaptation of HIRAID® Inpatient

A consensus-driven, real-time Delphi method with expert panel input will be used. Anonymous feedback will be provided during data collection, rather than after each Delphi round, improving efficiency and achieving consensus comparable to conventional Delphi studies [15, 16].

Aim: to adapt the HIRAID® emergency nursing framework for use in the inpatient care setting to assist in the assessment, management and delivery of person-centred and culturally safe inpatient care.

#### Participants

The expert panel will be purposefully recruited, and will consist of frontline hospital inpatient nurses, managers, physicians, surgeons, cultural safety academics, allied health clinicians and consumer investigators, representing those involved in delivering and receiving care. Given the relatively narrow scope and aim of this survey, and assuming a 20% attrition rate, this study will aim to recruit approximately 50 participants.

Participants will be selected from the investigation team (Principal or Co-Investigator) for their expertise in nursing, medicine, pedagogy, education and training, research, cultural safety, clinical governance, behaviour change, and expertise in the HIRAID® nursing framework. Additionally, key stakeholders nominated by hospital executives, such as experienced RNs from study wards, as well as patients and carers, will also be included. Prior to completing the Delphi survey, participants will attend a 30-min virtual education session on HIRAID® Inpatient. This session will summarise the framework and provide an opportunity for roundtable discussion and reflection.

#### Data collection

The Delphi survey will be informed by a review of current policies, education and orientation practices, and documentation templates collected from included inpatient hospital wards. The survey will also draw on the HIRAID® framework, and a Delphi survey previously used to adapt HIRAID® for aged care settings [17]. Roundtable discussions during panel preparation will provide additional input for survey development and an opportunity to develop a pilot version of the HIRAID® Inpatient framework.

Input from the expert panel will be collected using online surveys over three months. The survey will comprise nine sections, a short demographic questionnaire and one section for each of the eight elements of the original HIRAID® framework (Fig. 1). During each Delphi survey round, panel members can review anonymised real-time responses, including vote distributions, comments, and answers to open questions.

The Delphi survey will be hosted on *Calibrum*™ (Calibrum International, USA, calibrum.com), a secure web-based application for data management and survey tools. Each round of the Delphi survey will involve distributing three emails to eligible participants: one initial invitation when the survey opens, one reminder email one week after the initial invitation and one final reminder email two days before the survey closes. Participants will have two weeks from the first invitation to consider participation and then complete and return the survey.Round 1: A pilot version of the HIRAID® Inpatient framework will be distributed, along with a series of open questions to prompt experts to identify key areas for framework modification and adaptation. Responses from the first round will be summarised using content analysis and a de-identified report will be redistributed to participants prior to Round 2. Round 1 results will inform the framework and items in the subsequent round.Round 2: The second round will present a series of proposed framework changes, and the panel will be asked to rank their agreement for each item on a 5-point Likert scale. The responses will again be summarised and reported back to participants.Round 3: Based on the outcomes of Round 2, a third and final survey round will be conducted refining the framework further and confirming panel consensus.

#### Data analysis and outcomes

Data will be exported from *Calibrum*™ into SPSS V28™ (IBM Corp., Armonk, NY, USA) to obtain basic summary and descriptive statistics for demographic and other quantitative data [18]. Descriptive statistics will be used to summarise sample characteristics and outcomes, and further statistical tests will be conducted to ensure the sample is representative of the members of the panel based on demographic characteristics. Qualitative data will be exported to NVivo 14 (Lumivero, Denver, CO, USA) for content analysis, where responses will be analysed by at least two members of the research team and organised into categories and themes [19].

The level of consensus for each item will be calculated using a content validity index (CVI = number of respondents that agree/total respondents). Predefined levels of consensus (high, moderate, low) will be determined prior to the study: high consensus will be defined as ≥ 70% agreement, moderate consensus as 50–69% agreement, and low consensus as < 50% agreement. Items achieving high consensus will be integrated into the HIRAID® Inpatient framework.

### Phase 2: Explanatory sequential mixed methods study to design HIRAID® Inpatient implementation strategy

#### Study design

This explanatory sequential mixed methods study will deploy behaviour change theory-informed surveys of nursing staff to determine “who needs to change what” to implement HIRAID® Inpatient. Surveys will be followed by a series of focus groups with self-nominating nurses to further explore the barriers and enablers to HIRAID® Inpatient implementation. Quantitative and qualitative findings will be integrated and analysed using the Theoretical Domains Framework (TDF) and Behaviour Change Wheel (BCW) to develop an evidence-informed, modifiable implementation strategy for each cluster. This approach has been successfully used in trials based in the ED [13].

#### Participants and eligibility criteria

##### Nursing staff

The nursing workforce includes enrolled nurses (ENs), RNs, Nurse Units Managers (NUMs), Clinical Nurse Consultants (CNCs), Nurse Practitioners and Clinical Nurse Educators (CNEs). Permanent inpatient nurses (full/part time) and casual staff on the study wards will be invited to complete the survey. Agency nurses will be excluded, due to varying degrees of corporate knowledge, organisational governance and procedural familiarity. Email invitations to participate will be distributed by NUMs.

#### Data collection

##### Survey

Four emails will be distributed to eligible participants: an initial invitation when the survey opens, and weekly reminders until the survey closes. Participants will have four weeks from the first invitation to consider participation and to complete the survey. After completing the electronic survey pre-intervention, nurses will be invited to participate in a focus group discussion with a member of the research team to gather insights on their perceptions of the intervention and implementation enablers/barriers to HIRAID® Inpatient.

##### Focus groups

Semi-structured focus groups with consenting nurses will be conducted to deepen understanding of barriers and enablers to HIRAID® Inpatient implementation. This method is commonly used in health research to gain greater insight into complex phenomena [20]. Four to six focus groups (or until data sufficiency is reached) will be completed for each cluster, with an anticipated four to eight participants per group. The focus groups will take place in a private room away from the clinical area to minimise distractions while allowing clinicians to quickly return to the clinical area in case of an emergency. A semi-structured interview guide will consist of predetermined closed and open questions but will also enable the facilitator to ask additional questions that arise during the interviews. Interview questions will include nurses’ assessment and escalation processes, as well as perceptions of communication. Sessions will be audio recorded and transcribed verbatim. A facilitator will take field notes during the session if indicated. Two facilitators will attend each focus group.

#### Statistical methods

##### Survey

Data will be exported from REDcap™ into SPSS V28™ (IBM Corp., Armonk, NY, USA) to obtain basic summary and descriptive statistics for demographic and other quantitative data [18]. Descriptive statistics will be used to summarise sample characteristics and outcomes, and further statistical tests will be considered to ensure the sample is representative of the members of the panel based on demographic characteristics.

##### Focus groups

Qualitative data from free text survey comments and focus groups will be exported to NVivo for content analysis, where responses will be analysed by at least two members of the research team. Focus groups will be transcribed verbatim and original recordings permanently destroyed once the transcription is complete. Transcripts will be analysed and organised thematically and stored and managed using NVivo 14 (Lumivero, Denver, CO, USA) [19]. Thematic analysis will be guided by Gibbs’s framework [21] which includes: 1) transcription and familiarisation; 2) code building; 3) dis/confirmatory theme development; and 4) data consolidation and interpretation. The analysis framework provides a systematic approach to interpretation [22, 23]. All data sources will be triangulated to identify confirmatory and dis-confirmatory findings relevant to the patient safety climate. Triangulation of data will assist in the interpretation of findings.

##### Integration

The quantitative and qualitative data will be analysed and synthesised to identify consistent patterns and discrepancies. Categorical questions with a response rate of 70% or higher will be classified based on their wording; negatively worded questions will be labelled barriers and positively worded questions will be labelled enablers [24, 25]. The results will be integrated to derive the final barriers and enablers to HIRAID® Inpatient implementation. Barriers decrease the chance of the desired behaviour being performed while an enabler increases the chance of the desired behaviour being performed [25]. Qualitative responses will be categorised and used to confirm or refute the barriers and enablers identified in the quantitative data.

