##### Implementation study design

Once integrated, the new findings will be mapped to the TDF to enable a comprehensive, targeted theory-informed approach to the development of the implementation strategy [26]. The TDF is used to identify determinants of behaviour and provide comprehensive and systematic approaches to intervention implementation [26]. The mapped TDF domains will be integrated into the BCW, through linking to intervention function(s). The BCW is a validated series of tools for developing behaviour change interventions and is shown to improve the sustained success of clinical interventions [27]. Intervention functions form part of the BCW and are designed to influence behaviour by addressing capability, opportunity, and motivation [27]. If items cross multiple TDF domains and/or intervention functions, the research team will resolve this through a discussion, led by a senior member of the research team with extensive experience in the use of the TDF and behaviour change theories (lead author). The final implementation strategy will be refined using behaviour change techniques taxonomy and the APEASE criteria (Acceptability, Practicability, Effectiveness, Affordability, Spill-over effects, Equity) [28].

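### The Phase 2 survey rule labels items as barriers or enablers from their wording and a 70% response rate, without using the direction of nurses' answers

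*Protocol article*

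**What the plan says.** The rule is in the protocol article under Phase 2, Statistical methods, Integration. It has a filter and a label:

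- Filter: "Categorical questions with a response rate of 70% or higher will be classified based on their wording".
- Label: "negatively worded questions will be labelled barriers and positively worded questions will be labelled enablers".

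The same section defines the two terms by their effect on behaviour: "Barriers decrease the chance of the desired behaviour being performed while an enabler increases the chance of the desired behaviour being performed".

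It also provides a later check: "Qualitative responses will be categorised and used to confirm or refute the barriers and enablers identified in the quantitative data". The preceding Focus groups section under Statistical methods adds triangulation of all data sources. On the source of the qualitative data, the Phase 2 Study design section says "Surveys will be followed by a series of focus groups with self-nominating nurses". The Focus groups section under Data collection plans between four and six such sessions in every cluster, or as many as sufficiency of the data requires, and expects four to eight nurses at each. Free-text survey comments are also used.

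On what happens next, the Implementation study design section says "Once integrated, the new findings will be mapped to the TDF". From there the findings go to the Behaviour Change Wheel (BCW). The stated purpose is "to develop an evidence-informed, modifiable implementation strategy for each cluster".

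**The concern.** A survey item shows a barrier or an enabler only when its wording is combined with the answer. Disagreement with a positive statement and agreement with a negative one both point to a barrier. The rule as written uses the wording and the amount of response, and leaves the answer out. An item can therefore receive a provisional label opposite to what nurses reported, and an evenly divided item can receive a label at all.

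At stake is the survey's contribution to the implementation strategy. In an explanatory sequential design the survey comes first and the focus groups explain it. If the survey labels do not reflect the answers, the qualitative arm starts from a list that partly reproduces the questionnaire's phrasing. Fidelity scoring in Phase 3 may not reveal this, because facilitators score how fully the planned mechanisms were delivered, not whether they addressed the right problems.

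**Working it through.** The plan gives no figure to reproduce here. The check applies the written rule to hypothetical items and compares each label with the section's own definition.

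**Inputs from the protocol article**
- Threshold of 70%, described as a response rate, with numerator and denominator undefined (Integration).
- Label set by wording (Integration).
- Barrier and enabler defined by effect on behaviour (Integration).
- In Phase 1, Data analysis and outcomes, a 70% threshold is expressly one of agreement.
- 1259 nurses on the study wards (Study setting).

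**Assumptions**
- 85% of nurses answer the item. Any value of 70% or more gives the same result under the literal reading; any value below 70% gives no label.
- Answers divide into agree and disagree, so the share disagreeing is 1 minus the share agreeing.
- An answer is decisive when at least 70% agree or at least 70% disagree.

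**Three readings of the threshold**
- Literal: the share of nurses who answer the item.
- Agreement: the share who agree with it.
- Same answer: the share giving any one answer, that is, the larger of agree and 1 − agree.

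| Wording | Agree | By the definition | Literal | Agreement | Same answer |
|---|---|---|---|---|---|
| Positive | 10% | barrier | **enabler** | no label | **enabler** |
| Positive | 20% | barrier | **enabler** | no label | **enabler** |
| Positive | 50% | neither | enabler | no label | no label |
| Positive | 80% | enabler | enabler | enabler | enabler |
| Positive | 90% | enabler | enabler | enabler | enabler |
| Negative | 10% | enabler | **barrier** | no label | **barrier** |
| Negative | 20% | enabler | **barrier** | no label | **barrier** |
| Negative | 50% | neither | barrier | no label | no label |
| Negative | 80% | barrier | barrier | barrier | barrier |
| Negative | 90% | barrier | barrier | barrier | barrier |

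Bold marks a label opposite to the definition. Of these ten items:

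- Literal: 4 reversed, 2 labelled although divided, 4 right.
- Agreement: none reversed; the 4 decisively rejected items are left unlabelled, 4 are right, and the 2 divided items are properly left alone.
- Same answer: 4 reversed, 4 right, and the 2 divided items left alone.

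The counts reflect the grid chosen. They do not estimate how many real items are affected.

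**Denominator.** How many items pass the literal filter cannot be determined. If the base were all 1259 nurses, 0.70 × 1259 = 881.3, so 882 answers would be needed. If the base were those who returned the survey, the requirement could be far smaller. The article does not say which applies.

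**Size of the qualitative check.** The planned groups give 4 × 4 = 16 to 6 × 8 = 48 participants per cluster, all self-nominated, plus free-text comments. No step is described in which each labelled item is taken back to these data. The check is directed at barriers and enablers that the survey has identified, so an item left unlabelled under the agreement reading is not clearly within it.

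**The case against.** The strongest reply has three parts.

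First, the survey labels are provisional. The Integration section looks for discrepancies between the two data types, derives the final barriers and enablers from the integrated results, and lets qualitative responses overturn a label. What reaches the Theoretical Domains Framework (TDF) is the integrated finding, and the strategy is then refined with the behaviour change techniques taxonomy and the APEASE criteria. This stands, and it limits the harm. It does not repair the rule, because the check is not stated item by item and rests partly on volunteers.

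Second, response rate may be loose wording for the share endorsing the item. The rule would then be coherent for endorsed items and would reverse nothing. This may be the intention, but the article cannot settle it: the two sources cited for the rule are not available here, and Phase 1 uses the word agreement where agreement is meant. Even on this reading, decisive rejection of a positive item, which is direct evidence of a barrier, receives no label. The focus groups might still raise it independently.

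Third, this is formative work. That is correct: the Phase 3 outcome analyses, error rates and power do not depend on it.

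A reader might go further and infer that nearly all items pass the filter, that every item with majority disagreement is certainly mislabelled, or that wrong labels enter every cluster's strategy. The article supports none of these. The first needs high item completion and a denominator that is not given. The second fails under the agreement reading, and for items below the filter. The third overlooks the integration step; all clusters are exposed to the same rule, but error in each is not shown.

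**Conclusion.** The point holds as a defect in a stated rule. Read literally, or as 70% giving the same answer, the rule can assign provisional labels opposite to the section's own definition. Read as 70% agreement, it reverses nothing but leaves decisively rejected items unclassified. Each of the three readings needs correction.

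The size is modest and cannot be put as a number, since neither item wordings nor answer distributions are given. The qualitative check and triangulation reduce the risk without removing it. The consequence is confined to how well each cluster's strategy is targeted. A weaker intervention effect in Phase 3 is possible but would be conjecture.

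The conclusion rests on the sentence as printed. The percentages in the table are illustrative, and 70% as the mark of a decisive answer in either direction is an assumption carried over from the plan's own threshold.

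**What to change.** Replace the classification sentence with a rule that uses wording and direction together, for example:

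*Among nurses who answer an item, the item is an enabler if at least 70% agree with a positively worded item or disagree with a negatively worded one. It is a barrier if at least 70% disagree with a positively worded item or agree with a negatively worded one. All other items are mixed and are resolved with the qualitative data. Qualitative data are used to confirm or refute the classification of every item.*

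This drops the term response rate, fixes the denominator as item respondents, and keeps the existing qualitative check for labelled and mixed items alike. Applied to the ten items above, it gives the definition's label for the eight decisive items and mixed for the two divided ones. That agreement is by construction, since the same 70% is used for both. Using 70% for disagreement mirrors the existing threshold; the investigators may prefer another value if they state it in advance.

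The cost is one sentence. No new data are needed where items use an agreement scale, because the direction of each answer is already recorded.
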